**Workstream 1c: Self-Determination Theory Behaviour Change Framework**

In Workstream 1c, we seek to address the following research question: “What behaviour change model can be applied to optimise light exposure among older adults and promote sustainable behaviour change in this population?”

Following the evaluation of various behaviour change strategies such as the Health Belief Model, Theory of Planned Behaviour, and The Transtheoretical Mode, the Self-Determination Theory (SDT) stands out as a prominent framework for understanding and promoting behaviour change in older adults, given its foundation in motivation and well-being, its wide use, along with the growing evidence of efficacy.
^
82,
83
^ Additionally, the SDT has particular relevance and effectiveness in addressing older adults. Its emphasis on autonomy and empowerment aligns well with the needs and preferences of this population, making it a suitable framework for promoting healthy behaviours and enhancing well-being in older age.
^
84
^ The SDT was thus selected as the theoretical framework to guide the development of intervention and behaviour change strategies.

The SDT posits that human motivation is driven by three basic psychological needs: autonomy, competence, and relatedness. Individuals are intrinsically motivated to engage in activities fulfilling these needs, leading to greater persistence, satisfaction, and well-being.
^
85
^ To exemplify, a study by Teas et al. posits that merely encouraging and partaking in physical activity was insufficient to improve well-being in older adults. It was emphasised that these activities must also fulfil their psychological needs.
^
86
^ Extensive research has shown the effectiveness of interventions based on the SDT in health promotion, education, and workplace performance.
^
87–
91
^ Additionally, resources are available that elucidate the principles of the SDT and provide guidance for its application within the context of health, promoting and encouraging its utilisation.
^
67,
92
^

When applied to the context of light exposure, the SDT offers valuable insights into the motivational factors that can drive individuals’ light-related behaviours. The LightSPAN Behaviour Change Model framework is formulated based on the insights derived from the SDT, as shown in
Figure 2. The framework outlines the concepts by which we seek to foster autonomy, competence, and relatedness among participants, facilitating behaviour change in the context of light exposure.

**Figure 2. f2:**
[figure not shown]
Application of the Self-determination theory (SDT) in the LightSPAN project Behaviour Change Model framework, serving as a working model for this project.

In this framework, autonomy emphasises empowering individuals to make informed choices about their light exposure. This involves highlighting the importance of light for health and well-being and enabling participants to align their behaviour changes with their personal lifestyles and routines. By giving them control over implementing these changes, the intervention fosters a sense of ownership, making it more likely that participants will sustain their behaviour long-term.

Competence focuses on providing participants with the tools, education, and support needed to manage their light exposure effectively. This includes practical resources like light sensors and the LightSPAN mHealth app, which help participants track and adjust their exposure. The intervention also focuses on building knowledge, raising awareness of the benefits of optimal light exposure and equipping participants with the necessary skills to apply this knowledge. Additionally, tailored support ensures they have guidance to manage their progress confidently. This creates a sense of achievement and mastery as participants learn and apply new skills.

Relatedness is addressed by fostering a sense of care, respect, and connection between participants and the intervention team. Through collaborative co-design, participants’ feedback and preferences are considered, making them feel valued and understood. The language and interactions used are friendly and compassionate, encouraging a positive and respectful atmosphere that supports participant engagement. This principle also ensures that the participants feel connected to the broader goals of the intervention and the community.

The intervention will incorporate a series of techniques—self-monitoring, goal setting, feedback, and education—that are integrated to align with SDT principles of autonomy, competence, and relatedness. These techniques have been proposed to engage participants with technology and produce the desired behaviours. They have been shown to be effective in digital interventions across various studies,
^
93–
97
^ particularly in supporting self-efficacy and positively impacting behaviour.
^
98,
99
^ These techniques will work together within the LightSPAN mHealth app to create a cohesive and supportive intervention experience:
▪Self-monitoring empowers participants by giving them real-time data on their behaviour, allowing them to take control of their light exposure and make adjustments.▪Goal setting helps participants personalise objectives, breaking changes into achievable steps that foster confidence and a sense of progress.▪Feedback reinforces this progress by providing supportive insights and creating a caring environment that motivates continued engagement.▪Education underpins these techniques, providing participants with the knowledge and skills needed to make informed decisions.

Together, these techniques foster a sense of empowerment, mastery, and connection, motivating participants to sustain long-term change by aligning their actions with their personal goals and feeling supported throughout the process.

**Workstream 1d: Evidence-based recommendations for designing mHealth Interventions for older adults**

Workstream 1d addresses the following research question: “What evidence-based recommendations can guide the design and implementation of mHealth interventions tailored to older adults?”

To ensure the efficacy of our mHealth interventions tailored to older adults, we explored mHealth studies and established best practices. This step aims to identify strategies that have effectively leveraged technology to address older adults’ health-related concerns. Through a review of the evidence, we searched for studies on digital and mHealth interventions and co-design studies involving older adults. From these studies, we extracted evidence-based recommendations to guide the design and implementation of our mHealth interventions. These recommendations were synthesised to inform our app’s development and design process, ensuring it aligns with practices conducive to promoting health among older adults.

The evidence-based recommendations will be infused into the intervention through these five broad categories: app features, engagement strategies, development methodologies, interface design, and support mechanisms, providing a structured framework to guide the design and implementation of the app suitable for older adults.

**Integrating insights**

After thorough reviews and analyses of the evidence and available literature, we integrate our insights to inform the initial development phase and systematically guide subsequent steps in our project. This process informs the intervention design, focusing on developing the LightSPAN mHealth app developed following the additional work in Workstream 2. We aim to develop and present an evidence-based prototype of the smartphone application that aligns with the objectives and framework of the LightSPAN mHealth intervention, tailored to the needs of our target audience, and positioned to effectively promote healthy ageing.

**Workstream 2: Co-design of the mHealth intervention**

Workstream 2 centres on the collaborative design process of the mHealth intervention. It involves a comprehensive exploration of participant characteristics and needs alongside the design elements of mHealth interventions. To achieve this, we employ a multi-pronged approach consisting of several data collection methods. The first group comprises community service providers to seek their experience and knowledge to provide their insights and feedback on the proposed intervention plan.

The second group comprises community-dwelling older adult participants who partake in telephone interviews, FGDs, and prototyping workshops.

As part of the development process, we will outline a Minimum Viable Product (MVP) of the LightSPAN mHealth app, specifying the core functionalities of the app. This MVP will serve as a baseline for the early development of the prototype, which will be iteratively built and refined based on feedback gathered throughout the co-design process. This version will be refined through focus group discussions, prototyping workshops, and feedback from participants.

These methodologies enable collaborative development of the LightSPAN intervention with the study team, ensuring the active involvement of older adults in shaping the app according to their needs and preferences.

**Workstream 2a: Consultation with community service providers**

The consultation with community service providers aims to gather insights and feedback on the proposed intervention plan tailored for older adults. Invitations will be extended to community service providers working at Lions Befrienders (LB), a social service agency in Singapore dedicated to providing care and support for older adults.
^100^ We will recruit from a pool of community service providers, comprising individuals in roles such as programme staff, centre managers, administrative staff, and those involved in service delivery, community engagement, or innovation, based on convenience, with no specific inclusion or exclusion criteria (except for ≥18 years of age). The consultation will be conducted as a focus group discussion, guided by a pre-developed topic guide. During the consultation, the research team will present the proposed intervention plan and seek feedback, suggestions, and insights regarding the plan’s relevance, feasibility, and potential impact within the community setting. The session will cover potential barriers and facilitators to implementation, strategies for engagement and recruitment of older adults, and any additional considerations. Feedback collected during the consultations will help identify areas for improvement and refinement of the intervention.

**Workstream 2b: Engagement with older adult participants**

*Study sample*

The study will involve community-dwelling older adults in Singapore recruited via purposive sampling. Participants will be recruited from two Active Ageing Centres (AAC) with the support of Lions Befrienders. The AACs are a drop-in social, recreational hub for older adults in the community in various neighbourhoods across Singapore. Upon recruitment, participants will receive a comprehensive information package containing an invitation letter, participant information sheet, consent form, and contact details of the research team. The target sample size for the co-design study is 20 older adult participants, guided by previous co-design studies.
^
101,
102
^ This sample will be divided into four groups of five participants matched in sex and age for the focus group discussions and subsequent prototyping workshop sessions. The participants and researchers will have no relationship prior to the study. Eligible participants will be recruited according to the inclusion and exclusion criteria, including smartphone use and demographic and mental and physical health parameters. The specific inclusion and exclusion criteria are outlined in
Tables 1 and
2 below. 

**Table 1. T1:** Inclusion criteria for participants.

Domain	Criterion	Assessment method
**Age**	≥60 years of age	Self-report
**Community dwelling**	Residing in Singapore, not currently institutionalized or residing in nursing homes	Self-report
**Mobility**	Capable of independent walking with or without assistive devices	Self-report
**Functional Independence**	Capable of functional independence	Lawton Instrument for Activities of Daily Living (IADL). Score > 8 for females, > 5 for males
**Language**	Proficiency in communication, reading, and writing in English	Self-report
**Smartphone use**	Own smartphones	Self-report
**Participation**	Not currently enrolled in other on-going research endeavors	Self-report

**Table 2. T2:** Exclusion criteria for participants.

Domain	Criterion	Assessment method
**Cognition**	Cognitive impairment	Montreal Cognitive Assessment (MoCA), score ≤ 26
**Mental health**	Depressive symptoms	Geriatric depression scale (GDS) short form, score > 5
**Physical disabilities**	Significant physical impairment impacting daily activities	Self-report
**Health status**	Current diagnosis that interferes with daily function, and presence of severe terminal illness and/or psychiatric conditions	Self-reported with Self-Administered Comorbidity Measure (SCM)
**Visual health**	Visual impairment, diagnosis of eye diseases	Self-report
**Auditory health**	Uncorrected hearing impairment	Self-report

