### Health variables

Participant’s overall health will be assessed to determine health status, cognitive function, mental health, and ocular health.
Table 3 presents the screening measures that will be administered for participant recruitment.

**Table 3. T3:** Screening measures for study participants.

Construct	Instrument	Administration and instrument details	Outcome
**Functional Independence**	Lawton Instrument for Activities of Daily Living (IADL), developed by Ref. 104	Participants will complete the Lawton IADL to evaluate an individual’s self-reported ability to perform instrumental activities of daily living. The scale assesses a person’s functional independence in more complex activities that are necessary for independent living in the community such as managing finances, preparing meals, shopping, doing housework, using transportation, handling medications, and using the telephone. A score of > 8 for females, > 5 for males indicated functional independence.	Calculation of IADL scores for evaluation of functional independence in activities of daily living.
**Comorbid conditions**	Self-Administered Comorbidity Measure (SCM)	The SCM is a self-reported questionnaire consisting of items assessing various medical conditions, such as hypertension, diabetes, heart disease, and cancer. Participants will indicate their diagnosis and if the diagnosis interferes with their ability to carry out daily life activities.	Identification of comorbid diagnoses and assessment of overall health status.
**Cognitive Functioning**	Montreal Cognitive Assessment (MoCA), developed by Ref. 105	The MoCA is a standardized cognitive screening tool comprising various tasks assessing different cognitive domains, including memory, attention, language, and visuospatial abilities. Trained staff will administer the MoCA to participants in a quiet and distraction-free environment. Scores will be calculated based on participants' responses, with scores ≤26 indicating possible cognitive impairment.	Calculation of MoCA cognitive function scores (score range: 0-30).

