**Mood**	Geriatric depression scale (GDS) short form, developed by Ref. 106	The GDS short form is a validated questionnaire designed to evaluate mood among older adults. The scale assesses depressive symptoms in older adults, encompassing various aspects of depression, including mood, motivation, energy level, social engagement, and cognitive functioning. The GDS short form comprises 15 items and scores will be calculated based on participants' responses, with scores of >5 indicating depressive symptoms.	Calculation of GDS scores (score range: 0-15).
**Ocular Health**	Self-report form	Participants are given a form to self-report any vision-related issues.	Identification of vision-related symptoms, eye conditions, and overall self-report ocular health status.

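### The IADL inclusion cut-off is strictly above 8 (women) and 5 (men) with no scoring stated; at one point per item no woman, and on a five-item male set no man, can qualify

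*Protocol article*

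**What the plan says.** Workstream 2b, Table 1 (inclusion criteria), requires functional independence, assessed with the "Lawton Instrument for Activities of Daily Living (IADL" scale, and sets the threshold as "Score > 8 for females, > 5 for males". Table 3, under Health variables, repeats it: "A score of > 8 for females, > 5 for males indicated functional independence".

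Table 3 describes the scale by examples of the activities covered: "managing finances, preparing meals, shopping, doing housework, using transportation, handling medications, and using the telephone". Its outcome entry reads "Calculation of IADL scores for evaluation of functional independence in activities of daily living", with no range. For two other screening instruments the same column does give one: "Calculation of MoCA cognitive function scores (score range: 0-30") for the MoCA and "Calculation of GDS scores (score range: 0-15") for the GDS.

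The target is 20 older adults. On grouping, the article says: "This sample will be divided into four groups of five participants matched in sex and age".

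**The concern.** Two features of the cut-off do not sit well together. It differs by sex, 8 against 5, and no reason is given. The natural explanation is that women and men are scored on different numbers of items, with 8 and 5 as the respective full scores. Yet the inequality is strict, so on that explanation the threshold lies one step beyond the top of the scale, and the person with no dependency at all is the one who just fails.

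All 20 older adults must pass this criterion. If the scoring is as the pair suggests, literal application leaves nobody eligible, or leaves only men, which cannot be squared with groups matched in sex unless every participant is male. Staff would then have to set the written rule aside, enrolling people who fail a stated inclusion criterion with nothing to say who should be let through. The article gives no scoring from which they could settle the question.

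**Working it through.** **Inputs from the protocol article.** Cut-off: score > 8 (women), > 5 (men), Tables 1 and 3. Activities named: seven, as examples, Table 3. Sample: 4 groups × 5 = 20, which agrees with the stated 20.

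**Inputs not in the article (assumptions).** Number of items and points per item. I take 5, 7 or 8 items and five scoring schemes to show the range.

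**Formula.** For k items each scored from a to b, the total runs from k × a to k × b. The eligible set is every whole-number total in that range above the cut-off.

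**Items scored 0 or 1**

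| Sex | Items | Range | Eligible totals |
|---|---|---|---|
| Women | 7 | 0-7 | none |
| Women | 8 | 0-8 | none |
| Men | 5 | 0-5 | none |
| Men | 7 | 0-7 | 6-7 |
| Men | 8 | 0-8 | 6-8 |

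To exceed 8 at one point per item, at least nine items would be needed. With 8 items for women and 5 for men, nobody qualifies. With 8 items for both, a man short of the full score by two points (8 − 2 = 6) is admitted, while a woman with the full 8 is refused.

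**Graded items, 8 for women and 5 for men**

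| Points per item | Women: range, eligible | Men: range, eligible | Where the cut-off lies |
|---|---|---|---|
| 0-2 | 0-16, 9-16 | 0-10, 6-10 | 8/16 = 5/10 = 50% of maximum |
| 0-3 | 0-24, 9-24 | 0-15, 6-15 | 8/24 = 5/15 = 33% of maximum |
| 1-3 | 8-24, 9-24 | 5-15, 6-15 | equals the minimum |
| 1-4 | 8-32, 9-32 | 5-20, 6-20 | equals the minimum |

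Where items start at 1, the rule excludes only the single lowest total for each sex. Where they start at 0, the lowest passing totals are 9/16 = 56% and 6/10 = 60% of the maximum (items 0-2), or 9/24 = 37.5% and 6/15 = 40% (items 0-3).

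**Effect of the sign.** On 0/1 items with 8 for women and 5 for men, replacing > by ≥ changes the eligible set from empty to one total per sex: 8 of 8 and 5 of 5. On that scoring, the inequality sign alone decides whether anyone is eligible.

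**Could the sign be a text-reading fault?** It is unlikely. The ≥ in the age criterion of Table 1 and the ≤ in the MoCA criterion of Table 2 both came through, and > appears in both tables for the IADL.

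**The case against.** The strongest reply is that the decisive figure, the scale maximum, is nowhere in the article. Tables 1 and 3 agree with each other, so there is no internal contradiction, and a journal article may leave scoring details and ranges to the full protocol or screening form. The absence of a range is therefore not a fault in itself. That is correct, and it makes the finding conditional.

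A reader might infer that the cut-off is unattainable however the scale is scored. The article does not support this. With items scored 0-2, 8 and 5 are the midpoints of ranges 0-16 and 0-10, and a strict inequality there is coherent and attainable. Nor can one say that a graded version would let nearly everyone through, since the article gives no score distribution.

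A reader might also take the seven named activities as the whole item list and fix the maximum at 7. The article offers them as examples, so the list may be incomplete. It still makes a count of nine or more items look unlikely.

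Finally, Table 1 states the criterion in words as functional independence and places the score under assessment method, so the intent can be read. The study is also a small, purposively sampled one with descriptive and thematic analysis, so no error rate or effect estimate is at stake. Both points lessen the harm. Neither tells screening staff what to do with a woman who scores 8.

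**Conclusion.** The point holds in conditional form. The article fixes a hard eligibility threshold, twice, with a strict inequality and without the scoring that would give it meaning. On the assumption of one point per item, no woman can qualify with up to eight items, and no man can on a five-item set. If men are scored on seven or eight such items, they qualify from 6 upward, and the eligible pool is entirely male. This reading is the most natural one, given the sex-specific 8 and 5 and the seven activities named, but the article does not establish it.

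Under the graded scorings examined with 8 and 5 items, the cut-off is attainable but sits at the minimum or at a third to a half of the maximum, which is a weak test of functional independence.

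This is more than a missing detail. On the likeliest scoring, following the stated rule empties the eligible set or admits only men. It should be settled before screening.

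**What to change.** State the IADL version, the number of items for each sex, the points per item and the score range in Tables 1 and 3, as is already done with ranges for the MoCA and GDS. Then reconcile the inequality with that range in both tables and on the screening form.

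If the version used is the 0/1 sex-specific one with maxima of 8 and 5, > must become ≥ for the criterion to be attainable. If it is another version, the cut-off needs to be checked against that version's range. In either case the sponsor should confirm the intended rule, because the article does not give enough to choose it.

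The cost is a wording change in two tables and one form, with a minor notification to the ethics committee. It needs no extra participants and no change to the analysis.

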### Setting

The data collection sessions will take place at the AACs designated by LB and will utilize dedicated discussion rooms. These rooms will be set up to ensure a conducive environment, prioritizing comfort, privacy, and minimal disruptions, ensuring optimal conditions for engagement with older adults.
^
103
^

